### Pilot study

A 3-month pilot study will be conducted before the main phase of the trial. The pilot is designed to assess limitations in the usability and appropriateness of the intervention and trial material. Main outcomes will be improvements to the electronic tool and trial material before the main phase of the study.

We will install the intervention tool into three pilot practices. These practices will take on the study procedures: briefly, having the list of those eligible produced, inviting patients to consultation, reminding non-attendees after one month, and having the screen reminders activated. We shall interview two patients and two staff (one general practitioner (GP) and one other member) per practice. These interviews will focus on the usability and appropriateness of the electronic tool and patient material. Finally, we will remotely extract outcome data approximately one month into the pilot to test the extraction system.

### Process evaluation

The process evaluation, running in parallel with the intervention phase, will produce important study outcomes. The process evaluation aims:

1. To examine patient and practitioner views of electronic reminder systems in primary care, and their impact on consultations and practice.

2. To investigate barriers and enablers to the successful take up of an electronic audit and reminder tool by primary care teams.

3. To explore any barriers to recommended prescribing in AF that persist after the use of an electronic audit and reminder system.

We will collate data on the responses made to the screen reminders throughout the intervention period (that is, option chosen in response to a screen message). This will be logged by the intervention tool, and accessed remotely after the intervention phase. These data will allow us to study the suitability of the reminders.

The core of the process evaluation will be qualitative work with GPs and patients in intervention practices. We shall carry out semi-structured interviews with 10 GPs and up to 30 patients (a maximum of 1 and 5 respectively per practice), stopping if data saturation is reached (see Additional files 2 and 3). Intervention practices will identify patients and GPs eligible for interview, namely those who have been in contact with the intervention. We seek GP interview participants with maximum variability across practice list size and the location of the practice.

Interview participants will give individual consent, in addition to practice consent. GP interviews will focus on their views about the software tool, concentrating on impacts of the screen reminders on the consultation process, how well the software promotes best practice prescribing and any persisting perceived barriers to prescribing. We shall interview patients who have had a consultation to discuss anticoagulation as a result of the trial, stratifying by whether attendance resulted from the invite letter or an opportunistic reminder. We seek patients views on screen reminders in primary care, for example their thoughts on the change of subject of the consultation that they create [16], and on opportunistic health promotion - compared to the systematic approach of the letters. Interview transcripts will be analysed thematically and entered into a specialist software package (NVivo 9). We will organise and analyse emergent themes using the method of constant comparison.

### Sample size calculation

We have powered the study to detect changes in one of the secondary outcomes - change in proportion with CHADS_2_ score ≥2 who are prescribed anticoagulants. This is a smaller group than the denominator for the primary outcome, hence the need for greater power, but is important given its prominence in the QOF. We estimate a sample of 46 practices will be needed for the trial, accounting for clustering, variation in cluster size and 10 percent withdrawals [24]. This will give 95 percent power to detect a relative difference of 25 percent in proportion of eligible people who are treated between the trial arms, at 5 percent significance level.

The cluster size (*m* - number of patients with CHADS_2_ ≥2 in each practice) is estimated at 54 (based on mean list size and AF prevalence in the QOF [25], and recent CHADS_2_ estimates [8]). There is no relevant estimate of minimum change due to intervention; therefore we assumed 25 percent relative increase based on preliminary discussions. We estimated baseline prescribing of 53 percent [8], therefore 66 percent at follow-up. Assuming an intra-class correlation coefficient (ICC) of 0.03 (using a published ICC for inappropriate prescribing in the elderly [26]) and coefficient of variation (*cv*) of cluster size of 0.6 (based on a sample of THIN data on file; mean AF patients per practice = 119, standard deviation = 72) we estimate the design effect to be 3.17 (1 + ((1 + *cv*[2]) *m* - 1) x ICC) [27]. The initial total sample size, ignoring clustering is 720 (total in both arms) [28], therefore 2,282 accounting for the design effect. Including a 10 percent withdrawal this equates to 46 practices.

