### Intervention

The intervention is an electronic software tool installed in practice clinical systems. The tool identifies patients with AF who are eligible for anticoagulants based on recent guidelines (NICE TA249) [19], and are not currently prescribed therapy. We have designed the tool to operate in the EMIS Web clinical system. The tool will identify eligibility by interrogating data held in patient medical records. The NICE TA249 eligibility criteria are operationalised using the relevant clinical codes (see Additional file 1). Given that some criteria defining eligibility (see below) may be poorly coded, the tool highlights (through screen messages) patients with suspected relevant diagnoses (diabetes, heart failure, or hypertension), based on other aspects of their medical record (detailed decision rules available from the authors). These must be addressed by the clinician, with the diagnosis either confirmed or rejected, before proceeding. For instance, in current practice, most patients with known, symptomatic heart failure will be on the QOF Heart Failure register, a register that requires echocardiographic evidence of reduced left ventricular ejection fraction or a diagnosis of heart failure by a cardiologist. It is very unlikely that a patient will be on this register if they have neither NYHA class 2 symptoms (or greater) nor echocardiographic evidence of a low ejection fraction. However, in cases not on the register but where clinical codes suggest they should be, this will be questioned using automatically generated screen messages. Similar decision rules apply to possible uncoded diabetes and hypertension. In addition, the tool requests clarification over the nature (thromboembolic or haemorrhagic) of past recorded strokes, where non-specific electronic codes have been applied to the record. This is important as the distinction has a very important influence on eligibility for OAC therapy. This clarification is obtained by responses to screen prompts and these responses will be collected during the study.

The tool has two components:

1. A search module that maintains a list of patients diagnosed with AF, highlighting the group eligible for anticoagulation under current recommendations and who are currently not prescribed OAC therapy. According to NICE TA249 [19] patients are considered eligible if they meet one or more of the following criteria:

••previous stroke, transient ischaemic attack or systemic embolism

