#### Secondary outcomes

Secondary outcomes include the following:

1. The proportion of patients with CHADS_2_ score ≥2 prescribed anticoagulants. CHADS_2_ is a commonly used scoring system for stroke risk in atrial fibrillation [8].

2. A record of inappropriate care or prescribing related to anticoagulation in patients with AF.

3. The incidence of stroke, transient ischaemic attack (TIA), or other major thromboembolism during the trial, in patients with AF eligible for OAC.

4. The incidence of major haemorrhage during the trial in patients with AF eligible for OAC.

The denominator for the primary outcome will be all of those eligible for OAC therapy at the end of the 6-month trial period. This will include those whose eligibility has arisen since the start of the trial, for instance through reaching the 65- or 75-year age thresholds, or through a new diagnosis of a condition relevant to eligibility. It is important that the size of the denominator population is not influenced by use of the tool, as this could lead to ascertainment bias. We will therefore exclude from the outcome denominator those whose eligibility has arisen during the study purely as a result of improved recognition of diabetes, hypertension, heart failure, or thromboembolic stroke by the AURAS-AF tool, as the control arm will not be influenced by this improved recognition (see ‘Intervention’ section above). This group will be identifiable through the recording of responses to screen prompts. Patients diagnosed with these conditions independently of the tool will not be excluded. Similarly, cases where an ‘Atrial Fibrillation Resolved’ code is applied (effectively removing the patient from the study population) will be retained in the denominator if this decision resulted directly from the use of the AURAS-AF tool in the intervention arm.

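### The rule against tool-driven changes in the denominator is tied to TA249 eligibility for the primary outcome, so it does not cover the CHADS2 ≥2 denominator on which the trial is powered

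*Protocol article*

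**What the plan says.** Sample size calculation: "We have powered the study to detect changes in one of the secondary outcomes". The outcome meant is anticoagulant treatment among patients scoring CHADS2 ≥2. The section adds: "This is a smaller group than the denominator for the primary outcome, hence the need for greater power". It follows that some TA249-eligible patients score below 2. Power is put at 95% for a 25% relative difference between arms, tested at the 5% level.

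Secondary outcomes (denominator paragraph): "The denominator for the primary outcome will be all of those eligible for OAC therapy at the end of the 6-month trial period". The paragraph says the tool must not influence the size of the denominator, because that could cause ascertainment bias. It then excludes patients whose eligibility arose during the study purely because the tool improved recognition of diabetes, hypertension, heart failure or thromboembolic stroke. It keeps patients given an AF Resolved code as a direct result of the tool. Diagnoses made independently of the tool count. No corresponding rule is given for CHADS2 ≥2.

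Intervention: "the tool highlights (through screen messages) patients with suspected relevant diagnoses (diabetes, heart failure, or hypertension". The clinician must confirm or reject each suspected diagnosis. The tool also asks whether past strokes with non-specific codes were thromboembolic or haemorrhagic. Age 75 or older is sufficient by itself for TA249 eligibility.

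Control practices: the software is installed but inactive, with no list and no reminders.

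**The concern.** The article recognises that a tool which improves coding can change who is counted in one arm only, and it writes a rule to stop this. The rule asks whether *eligibility* arose through the tool. For CHADS2 ≥2 the question that matters is whether the *score* crossed 2 through the tool, and the two can differ.

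Take a patient aged 75 or over with no other coded risk factor. That patient is TA249-eligible from the start and, on the usual scoring, has one CHADS2 point. If a prompt leads the clinician to confirm hypertension, diabetes or heart failure, the score becomes 2 and the patient enters the CHADS2 ≥2 denominator. Eligibility has not changed, so the exclusion does not act. An identical patient in a control practice gets no prompt and stays outside.

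The arms would then be compared on sets of patients that the intervention itself had altered after randomisation. ANCOVA on the baseline proportion does not remove this. Nor can it readily be repaired later: under Ethical considerations the team receives only anonymised pro forma data or data aggregated to practice level. The definition therefore has to be right in the extract.

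**Working it through.** **1. The plan's own figures.** Inputs from Sample size calculation: 53% against 66% (53% × 1.25 = 66.25%), m = 54, ICC 0.03, cv 0.6, 95% power, 5% significance (taken as two-sided), 10% withdrawal, 46 practices.

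- Total ignoring clustering, 53% v 66.25%: 708, or 738 with continuity correction. Stated: 720.
- Design effect: 1 + ((1 + 0.6²) × 54 − 1) × 0.03 = 1 + 72.44 × 0.03 = 3.173. Stated: 3.17.
- 720 × 3.17 = 2,282, as stated.
- Practices: 2,282 / 54 = 42.3. Dividing by 0.9 gives 46.95; multiplying by 1.1 gives 46.5. Stated: 46.
- Power after withdrawal: 46 × 0.9 = 41.4 practices; effective n per arm = 41.4 × 54 / 2 / 3.173 = 352. With power = Φ((d − 1.96·SE₀)/SE₁), SE₀ pooled and SE₁ unpooled, d = 0.1325 gives 94.9% (94.2% if 66% is used).

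The stated calculation reproduces.

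**2. Which denominator is protected against what.**

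| Tool-driven event | Primary denominator | CHADS2 ≥2 denominator |
|---|---|---|
| Prompted diagnosis makes the patient newly TA249-eligible | Excluded by rule | No rule stated |
| Prompted diagnosis in an already eligible patient takes the score to 2 | No change in membership | Patient enters; the primary rule would not act |
| Non-specific stroke clarified as haemorrhagic | May remove; no retention rule stated | May remove; no rule stated |
| AF Resolved code resulting from the tool | Retained by rule | No rule stated |

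**3. Illustration of size.** The documents give no recoding rate, so g and r below are assumptions. Let g be the growth of the intervention-arm CHADS2 ≥2 denominator and r the treated share of those added. The observed proportion is (0.6625 + g·r)/(1 + g), compared with 0.53. Power uses the formula above with effective n held at 352 per arm and no baseline adjustment.

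| g | r | Observed proportion | Difference (points) | Power |
|---|---|---|---|---|
| 2% | 0 | 64.95% | 12.0 | 90% |
| 2% | 30% | 65.5% | 12.5 | 93% |
| 5% | 0 | 63.1% | 10.1 | 78% |
| 5% | 30% | 64.5% | 11.5 | 88% |
| 10% | 0 | 60.2% | 7.2 | 49% |
| 10% | 30% | 63.0% | 10.0 | 76% |
| any | 66.25% | 66.25% | 13.25 | 95% |

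For scale, 5% of 54 is 2.7 patients per practice.

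**4. The bias has no fixed sign.** With no true effect (53% in both arms) and g = 5%, the spurious difference is (0.53 + 0.05r)/1.05 − 0.53. This is −2.5 points at r = 0 and +1.3 points at r = 80%. If the tool instead removed 5% of the denominator, all untreated, 66.25% would read 0.6625/0.95 = 69.7%.

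**The case against.** The strongest reply is that this is a detail of a secondary outcome in a condensed article. The denominator paragraph states a general principle, its exclusion refers simply to the outcome denominator, prompt responses are logged, and the full protocol or SAP may extend the rule. The prompts exist to settle eligibility; if the unseen decision rules fire them only where eligibility is open, the patient aged 75 or over never receives one. The article does not list the CHADS2 components. ANCOVA on baseline should also give a smaller standard error than the unadjusted one used here, so power would be higher than shown.

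Much of this stands. The components and the reach of the prompts are assumptions, although the Intervention section does not limit prompts to patients not yet eligible. The power figures are illustrative and unadjusted. Two points remain. The article does set out a denominator rule, and even read generously its trigger is eligibility, which is the wrong test for a score cut-off. And baseline adjustment improves precision but does not correct a change in who is counted.

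A reader might also infer that the CHADS2 ≥2 denominator necessarily grows in the intervention arm and dilutes the effect. The documents do not support that: suspected diagnoses may be rejected, strokes may be clarified as haemorrhagic, AF may be coded as resolved, and entrants may be treated at any rate.

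**Conclusion.** The point holds as a gap in the definition of the powered outcome. The stated protection is worded for the primary denominator and keyed to TA249 eligibility, so it does not cover CHADS2 ≥2. If CHADS2 has its standard components and prompts reach already eligible patients, tool-prompted coding can move patients across the cut-off in the intervention arm only. Direction and size cannot be determined from the article. The illustrative loss at 5% growth with 0–30% of entrants treated is about 2 to 3 points of a 13.25-point difference (13.25 − 11.5 = 1.75; 13.25 − 10.1 = 3.15), and there is none if entrants are treated at the arm's own rate.

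This does not show that the sample size is miscalculated or that the primary outcome is compromised. The sample size reproduces, and the primary outcome's own rule is not in question here.

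**What to change.** For CHADS2 ≥2 only, state in the outcome definition and build into the data extract that:

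- patients whose score reaches 2 purely through a logged tool prompt are excluded from the denominator; and
- patients whom the tool removes, through an AF Resolved code or a stroke reclassification, are retained.

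This follows the article's existing principle and uses the prompt responses that it already plans to record.

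Alternatively, score CHADS2 in both arms from diagnoses coded before day 0, updating only age to month 6, and report the as-coded 6-month version as a sensitivity analysis. This treats the arms identically and does not depend on attributing codes to prompts. Its small cost is that true new comorbidity within the 6 months does not update the score.

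Either option needs a sentence or two in the outcome definition and a matching filter in the extract, set before data are drawn because the team receives aggregated counts. Leave the primary outcome's rule as it is, including its deliberate choice to count diagnoses made independently of the tool.

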### Ethical considerations

As a cluster randomised trial, with practices as participants, the trial has specific ethical considerations. We seek informed consent to participate from the practices, with a practice ‘guardian’ consenting to trial entry [21,22] on the basis that the guardian will act for the good of the cluster; benefits and harms of entry to the trial will not exceed non-entry and the intervention will not be too onerous or contentious for cluster members [22]. Interview participants will give individual informed consent. We shall use data from the primary care medical records; however we will only receive anonymised *pro forma* data or data aggregated to a practice level. Finally, we shall employ a data monitoring committee to monitor study progress for safety, notably the secondary outcomes (inappropriate prescribing, stoke, TIA, and haemorrhages).

The study protocol and associated material have received a full favourable opinion from the NRES Committee South Central - Berkshire (REC number 13/SC/0026); and national NHS research and development approval. We have registered the trial on the International Standard Randomised Controlled Trial Number Register (ISRCTN55722437) and the UK Clinical Research Network portfolio. We have developed the full study protocol in line with SPIRIT guidelines (full protocol available on request) [29], and will conduct and report the trial in line with the CONSORT extension to cluster randomised trials [24].

## Discussion

AURAS-AF investigates whether a reminder intervention, using electronic primary care records, can safely increase anticoagulant uptake in a high stroke risk group with AF. This has been recognised as an important area for stroke prevention, and one that has lagged behind improvements in other areas of stroke care [8,30]. A number of barriers to anticoagulation have been proposed, however, their precise importance remains unclear [12]. Given the relative complexity of stoke risk scoring tools, and recently changing guidelines for anticoagulant eligibility, clinician uncertainty may play a role [14]. The use of automated tools that harness electronic data in primary care may clarify which patients with AF are eligible for OAC and flag this risk during routine care.

Electronic reminders are now commonplace in UK primary care, but the evidence to support their use is disproportionately low. Few have been assessed in randomised trials [31,32], and questions remain as to whether the quality of the underlying data is sufficient to risk assess patients for serious outcomes [8,33]. The evidence behind consultation based reminders is especially important when considering their potential for harm, or more specifically their disruptiveness and/or irrelevance to the clinical problem at hand. It has been proposed that such reminders may reduce patient autonomy; lengthen consultations excessively; and lead to clinician reliance [16-18]. Finally, for AF, the prompts could rush clinicians into unsafe prescribing. There is little substantive evidence to support, or dispel, these concerns. Our process evaluation of the AURAS-AF intervention will provide valuable data, especially qualitative, on the safety and suitability of electronic reminders in this area of care. We anticipate that prescribing may in fact be safer through use of the tool - with the most recent national eligibility criteria applied systematically to patient data - but this assumption requires confirmation though this research [19]. Reports of inappropriate prescribing in the study will therefore be important outcomes.

Finally, the AURAS-AF trial will test a relatively new approach to conducting primary care research. Recent studies have utilised primary care databases to facilitate randomised controlled trials [32,34]. We will use the capabilities of a web-based clinical system both to deploy a primary care intervention and to collect outcome data. There has been a very recent move to generate data for cross-sectional analyses through the anonymous extraction from medical records via this method [35,36]. Use of this extraction process for a randomised trial may substantially reduce costs of data collection and provides a novel platform for the study of interventions and processes of care in a range of clinical areas.

## Trial status

The intervention tool has been developed and the pilot study began on 21 June 2013. Recruitment for the main phase began on 1 July 2013, with an anticipated start date of 1 December 2013.

## Abbreviations

AF: Atrial fibrillation; EMIS: Egton Medical Information Systems; GP: General practitioner; ICC: Intra-class correlation coefficient; NICE: National Institute for Health and Clinical Excellence; NIHR: National Institute for Health Research; NRES: National Research Ethics Service; NYHA: New York Heart Association; OAC: Oral anticoagulant; PCRN: Primary Care Research Network; QOF: Quality and Outcomes Framework; TIA: Transient ischaemic attack
